Five weeks after the embryo transfer (that is, 7 weeks gestation by last menstrual period) the women will have a first pregnancy scan (this is a standard protocol for all our unit patients). This scan will check for the viability of pregnancy in the form of positive heart beat pulsations. At this point a pelvic Doppler will also be performed to determine the blood velocity in the uterine arteries (the main vessels which supply blood to the womb). This will enable us to compare the blood flow between the two treatment groups.

At this appointment, a further 15 ml venous blood sample will be taken to check for progesterone, estradiol, free beta-hCG, Inhibin A, Inhibin B, PAPP-A, and Activin A. Patients with a viable pregnancy as confirmed by an ultrasound will continue with the pessaries for up to 10 weeks post-embryo transfer (that is, 12 weeks gestation).as explained below:

Patients with a viable pregnancy at this point will be informed of the various antenatal screening methods available to them (that is, triple test, quadruple test, nuchal translucency, etc.) as per unit standard practice.

At the end of the week 10 post-embryo transfer (that is, 12 weeks gestation) the women will be asked to attend the unit for a further pregnancy scan to determine the viability of the pregnancy and record the fetal heart rate (FHR). At this appointment the second uterine artery Doppler is performed to compare the blood velocity between the two groups. A further 15ml venous blood will be taken to check for progesterone, PAPP-A, estradiol, free B-hCG, Inhibin A, Inhibin B and Activin A.

At approximately 34 weeks gestation a courtesy phone call will be made to the patient to enquire how the pregnancy is proceeding. This will be undertaken by the medical/research team heading the trial.

Following delivery, birth details and neonatal outcome will be observed.

Treatment allocation

1. Following a positive biochemical urinary pregnancy test, the patient will be asked to attend the reproductive unit if not present already. After eligibility has been confirmed the patient will be asked to sign the trial consent form. This will be done by a member of the Hewitt Centre Staff who is trial trained and GCP compliant.

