## Discussion

### Measure of outcomes

Primary outcome measure:The primary outcome measure is the proportion of all randomized women that continue successfully to a viable pregnancy (at least one fetus with FHR >100 beats/minute) on transabdominal/transvaginal ultrasound at 10 weeks post-embryo transfer/12 weeks gestation (that is, at the end of 8 weeks supplementary trial treatment). The following clinical estimates are available. The success rate at the biochemical testing stage is approximately 32.5%. Currently, without further progesterone supplementation, 80% of these women will carry on successfully with a viable pregnancy (25.8% of clinical pregnancy rate) whilst 20% of these women will miscarry. We anticipate that an increase of 10% from the biochemical to the clinical pregnancy rate would be clinically important and therefore justify an additional 8 weeks supplementation with progesterone, in other words, a reduction of 10% in the miscarriage rate.

Secondary outcomes:

1. Viable pregnancy (at least one fetus with FHR > 100 beats/minute) on transvaginal ultrasound at 5 weeks post-embryo transfer/7 weeks gestation (that is, at the end of 3 weeks supplementary trial treatment).

2. Relationship of serum markers (estradiol, progesterone, Inhibin A, Inhibin B, Actavin A, free beta-hCG and PAPP-A) taken at 5 and 10 weeks post-embryo transfer with treatment allocation, primary outcome and secondary outcomes.

3. A pelvic Doppler will be performed to determine if the blood velocity in the uterine artery is different in the two groups. This will be performed at 5 and 10 weeks post-embryo transfer.

4. Side effects

A visual analogue score relating to the following side effects will be completed at both 5 weeks and 10 weeks post-embryo transfer: nausea, bloating, vaginal discharge and vaginal irritation.

5. Antenatal Down’s Screening Outcomes

Antenatal Down’s screening results for all patients will be monitored, including individual serum quantification for double, triple, quadruple screening and nuchal translucency.

6. Neonatal outcomes

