#### Data collection

Information will be collected at the following times:

Trial entry (from clinical notes)

At 5 weeks post-embryo transfer – following a fetal ultrasound scan to determine viability of the pregnancy and uterine artery Doppler parameters (from clinical notes).

At 10 weeks post-embryo transfer – following fetal ultrasound scan to determine the viability of the pregnancy and uterine artery Doppler parameters (from clinical notes).

Serum results will be returned in batch form at the end of the trial directly to the case report file.

Antenatal screening results (Each patient is given a standard form with self-addressed stamped envelope at the second ultrasound scan to be completed following antenatal screening). Data will be entered directly to the case report file.

The outcome of the pregnancy will be recorded after delivery. Each patient is given a standard letter which is to be completed after delivery. Data can also be obtained from the reproductive centre database (HFEA requirement). Information regarding delivery will also be recorded in the clinical case notes.

A neonatal assessment will be performed shortly after delivery by a member of the neonatal team in the delivery hospital. Each patient is given a standard form with self-addressed stamped envelope at the second ultrasound scan which is to be returned with the delivery details.

There may be a long-term follow-up of all the live births in the trial.

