#### Primary outcome

The primary outcome (proportion of viable pregnancies) will be summarized with a relative risk and 95% confidence interval. The primary analysis will be logistic regression taking into account the age of the woman (that is, the stratification variable).

If other important prognostic factors are imbalanced between the two groups the robustness of the findings will be investigated by including other covariates in the logistic regression.

Although it is anticipated that withdrawal rates will be low, there may be missing values. A range of clinically plausible scenarios will be used to impute missing values in order to test the robustness of the findings. Details of this will be approved by Data Monitoring Committee (DMC) once the magnitude of the problem is known. The statistician may need to be unblinded for these analyses in order to carry out realistic, conservative analyses.

The effect of compliance (as a suitably coded factor) will be investigated by testing the interaction between treatment group and compliance.

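### A missing 12-week viability result should first be derived, blind to allocation, from pregnancy outcomes the trial already plans to record, with scenario imputation kept for women still unresolved

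*Protocol article*

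**What the plan says.** In the protocol article, Measure of outcomes defines the endpoint over everyone randomized: "The primary outcome measure is the proportion of all randomized women that continue successfully to a viable pregnancy", judged by ultrasound at 10 weeks post-transfer (12 weeks' gestation).

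The Primary outcome paragraph of the Analysis section expects few withdrawals but allows for missing values. Its stated handling is: "A range of clinically plausible scenarios will be used to impute missing values in order to test the robustness of the findings". On timing it adds: "Details of this will be approved by Data Monitoring Committee (DMC) once the magnitude of the problem is known". On blinding it adds: "The statistician may need to be unblinded for these analyses in order to carry out realistic, conservative analyses". The Trial statistician section repeats that unblinding may be needed for these sensitivity analyses.

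The article also describes other records of how each pregnancy fared:

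- **5-week scan** (Recruitment), standard for all the unit's patients: "This scan will check for the viability of pregnancy in the form of positive heart beat pulsations".
- **34-week contact** (Recruitment): "At approximately 34 weeks gestation a courtesy phone call will be made to the patient to enquire how the pregnancy is proceeding".
- **Delivery outcome** (Data collection), from a letter the woman completes and from clinical case notes. A further source is given: "Data can also be obtained from the reproductive centre database (HFEA requirement").

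Withdrawals says that a woman who stops treatment has not thereby left the study. No section links any of these records to a missing 12-week result.

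**The concern.** Pregnancy status runs one way. A pregnancy still ongoing at 34 weeks, or one that ended in delivery, had a living fetus at 12 weeks. A pregnancy wholly lost before 12 weeks did not. For this endpoint, then, a missed scan does not always mean an unknown answer.

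The stated handling goes straight to assumed values. It leaves their details open until the amount of missing data is visible, and it permits unblinding to set them. A rule based on recorded facts can be fixed beforehand and applied without knowing the arm. It would leave fewer women to whom assumptions must be applied, and less reason to unblind.

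Missingness may also be related to the outcome. A woman who has miscarried has little reason to attend a later viability scan. This is a reasoned possibility; the article gives no data on it.

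**Working it through.** **No figure to reproduce.** The article gives neither an expected missing rate nor a retrieval rate. The Analysis section says only that drop-outs should be minimal. What follows is an illustration on stated assumptions.

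**Inputs**

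- Rates among observed women: 80% control, 90% progesterone (the design rates in the Analysis section).
- N = 240 per arm: the ceiling of 480 randomized, halved.
- k = 10 missing per arm (assumption): the gap between 480 and the target of 460 is 20 women, and 20/480 = 4.2%.

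**Formula.** With k unresolved per arm and a true difference of 0.10 among the rest, the two extremes are

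0.10 × (N − k)/N ± k/N.

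The minus sign counts every unresolved control as viable and every unresolved treated woman as not viable; the plus sign is the reverse. The width is 2k/N and depends only on how many women remain unresolved. Confidence intervals are Wald: difference ± 1.96 × √[p₁(1 − p₁)/N + p₂(1 − p₂)/N].

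**Nothing resolved (k = 10).** Observed successes are 0.8 × 230 = 184 and 0.9 × 230 = 207.

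- Lower extreme: 194/240 v 207/240, difference 13/240 = 5.4 points (95% CI −1.2 to 12.0).
- Upper extreme: 184/240 v 217/240, difference 33/240 = 13.75 points (95% CI 7.2 to 20.3).

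**Half resolved (k = 5).** 0.10 × 235/240 ± 5/240 = 0.0979 ± 0.0208, so 7.7 to 11.9 points. The lower extreme has 95% CI 1.2 to 14.2.

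**Eight of ten resolved (k = 2).** 0.10 × 238/240 ± 2/240 = 0.0992 ± 0.0083, so 9.1 to 10.8 points. The lower extreme has 95% CI 2.7 to 15.5.

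The last two cases assume that resolved women have the same 80% and 90% rates, as expected counts. Other rates would move the centre of the range. The width would still fall from 20/240 = 8.3 points to 4/240 = 1.7 points when k goes from 10 to 2.

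**Other assumed missing rates,** at the planned 230 per arm with nothing resolved (p from the pooled two-proportion z-test at the lower extreme):

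| Missing per arm | Range (points) | p at lower extreme |
|---|---|---|
| 5 (2%) | 7.6 to 12.0 | 0.025 |
| 10 (4.2%) | 5.2 to 13.9 | 0.13 |
| 12 (5%) | 4.3 to 14.7 | 0.22 |
| 23 (10%) | −1.0 to 19.0 | 0.78 |

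At 10% missing, resolving about 80% (5 per arm left) brings the range back to 7.6 to 12.0 points.

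**What each source can settle**

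| Record | What it settles about 12 weeks |
|---|---|
| Ongoing at the 34-week contact, or a delivery from this cycle | Viable; heart rate above 100 is inferred |
| 5-week scan confirming loss of the pregnancy | Not viable |
| Loss documented and dated before 12 weeks | Not viable |
| Viable 5-week scan and nothing later | Unresolved |
| 5-week heart rate of 100 or below without confirmed loss | Unresolved |
| Loss without a date | Unresolved |

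**The case against.** The strongest reply is that the article contains no error here. A source hierarchy for a missed visit is ordinary analysis-plan content, the article openly defers detail, and nothing in it forbids using records. Clinically plausible scenarios are compatible with using them. This stands in part: the text is not contradictory. But the article does state a method, a timing and a licence to unblind, and a better method is available from data it already plans to collect.

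Three stronger readings are tempting, and the document does not support them:

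- **That guesses would replace known outcomes in the primary analysis.** The scenarios are described as a robustness check, and missing is never defined as having no 10-week scan.
- **That known miscarriages would be imputed.** The endpoint is a proportion of all randomized women, and Measure of outcomes sets the 20% who miscarry against the 80% who continue. A documented loss would naturally count as a failure.
- **That the records would settle most missing results.** Without a missing or retrieval rate this cannot be shown. The 34-week contact is a courtesy call and is absent from the Data collection list. The delivery letter depends on the woman returning it. Women who withdraw may be hard to trace, although the centre database is not described as needing their reply.

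The illustration is also a stress case. Opposite extremes in the two arms need not be among the plausible scenarios. With 5 missing per arm, even the lower extreme keeps its confidence interval above zero.

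Patient selection places follow-up in a range of hospitals, from which a reader might infer that well women miss the primary scan. Recruitment, however, asks women to attend the unit for it, so that reason is not shown.

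**Conclusion.** The point holds as an inexpensive improvement to the stated method. The only stated handling of a missing primary outcome is scenario imputation as a robustness check, detailed after the extent is known and possibly by an unblinded statistician. Records already planned would determine some of those results as fact; what share, the article does not allow anyone to say.

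The size is conditional. With 10 of 240 missing per arm and 80% v 90% among those observed, the extremes run from 5.4 to 13.75 points, and the lower one loses significance. If 8 of the 10 per arm are resolved at the same rates, the extremes run from 9.1 to 10.8 points and the lower one stays significant. If missingness is as small as the article expects, the gain is smaller.

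**What to change.** Add one paragraph to the Primary outcome analysis, adopted before allocation is revealed to whoever applies it:

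1. If the 10-week result is missing, derive it from recorded outcomes, blind to allocation and before any imputation.
2. Classify as viable when a pregnancy from this cycle is documented as ongoing after 12 weeks or as a delivery (34-week contact, case notes, delivery letter or centre database).
3. Classify as not viable when a loss dated before 12 weeks is documented, or the 5-week scan confirmed loss of the pregnancy.
4. Leave as unresolved a viable 5-week scan alone, a 5-week heart rate of 100 or below without confirmed loss, or an undated loss.
5. Use the derived values in the primary analysis, apply scenario imputation only to unresolved women, and report by arm how many were resolved by each source.

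The 34-week contact should also be added to the Data collection list so that its result is recorded.

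Cost: a paragraph and a look-up in records already planned. The drawback is some loss of exactness: women classified as viable by this route have a heart rate above 100 at 12 weeks inferred from the pregnancy having continued. Reporting the numbers by source lets readers judge this.

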#### Secondary outcomes

These will be exploratory analyses producing 95% confidence intervals. They will be unadjusted for multiple analyses. The interpretation will take multiple testing and the consequent likelihood of type I errors into account qualitatively.

Continuous outcomes will be analyzed by analysis of covariance and dichotomous variables by logistic regression. In a similar way to the analysis of the primary outcome, these analyses will stratify for age, and the robustness of findings will be examined by including other potentially important prognostic covariates. A range of plausible values will be imputed for missing values.

Where a large proportion of values are missing (typically >25%) only descriptive statistics will be provided.

If any variables are highly skewed, leading to doubts about the validity of the parametric analyses, non-parametric analyses will be carried out or bootstrapping will be used.

#### Demographics and other clinical variables

Other variables (for example, describing the groups at baseline or the clinical progress of the women) will be described using summary statistics only.

### Ethics

The DOLS trial has full ethical approval (REC 06/MRE08/17). Additional counseling will be offered from the research team for women with failed pregnancies.

### Data management

#### Data monitoring committee

For the trial a DMC has been established. This is independent of the trial organizers. Regular meetings are established for the duration of the trial with open and closed sessions so the DMC members can analyze the interim analysis data when required. The Trial Steering Committee (TSC) will provide the Chair of the DMC with any other analysis as is requested by the Chair.

If any other evidence from other randomized controlled trials is published during the running of the trial then the DMC will be fully informed by the TSC. With this evidence, and the interim analysis, the DMC will inform the TSC if the trial needs to stop.

All SAEs will be reported to the TSC, and in turn these will be reported to the DMC.

The unblinding of the trial is the responsibility of the Chief Investigator. Should any SUSAR be incurred the trial can be unblinded by a 24 hour telephone line within the pharmacy department. The on-call pharmacist has access to unblinding the trial.

#### Trial statistician

The trial statistician will be made aware of assignment to treatment codes (for example, A or B), but will remain blinded as to which is active ingredient or placebo. The trial statistician will be involved in the preparation of reports for DMEC. Unblinding may become necessary when invoking sensitivity analyses for missing values.

#### Data handling and storage

There is provision for dedicated personnel for the collation, storage and management of data, as provided by the Liverpool Womens’ Hospital Research and Development Trials office. Additional resources are available for data checking and double entry of data.

#### Direct access to source data/documents

The investigator(s)/institution will permit trial-related monitoring, audits, Institutional Review Board/regulatory inspections, providing direct access to source data and documents.

#### Monitoring

Monitoring will be the responsibility of the Research and Development Manager at Liverpool Womens’ NHS Foundation Trust Hospital.

#### Liability and negligence

The trust and investigators are not liable or responsible for harm encountered through participation in the trial. However, harm relating through action(s) of negligence are accountable through the trust. The National Health Service complaints mechanism is available to patients.

## Trial status

The trial has completed recruiting by the 1 June 2012.

## Abbreviations

DMC: Data monitoring committee; DOLS: Duration of luteal support; FHR: Fetal heart rate; GnRHa: Gonadotrophin releasing hormone agonists; hCG: Human chorionic gonadotrophin; hMG: Human menopausal gonadotrophin; IM: Intramuscular; IVF: in-vitro fertilization; LH: Luteinizing hormone; NHS: National health service; R&D: Research and development; SAE: Serious adverse event; SAR: Serious adverse reaction; SUSAR: Suspected unexpected serious adverse reaction; TSC: Trial steering committee.
